#### Study progression criteria

This study will include an internal recruitment pilot phase with stop-go recruitment milestone criteria to mitigate risk to the funder. This internal pilot will be used to confirm recruitment rates and aims to recruit the first 400 participants (almost one-fifth of the sample size) from 10 sites by the end of study month 13. By the end of study month 13, the aim is to have 400 participants (18%) enrolled with an average recruitment rate/site/month of at least five participants in the best 60% of sites, with at least 10 sites open (table 3).

**Table 3 T3:** Internal recruitment pilot study progression criteria

By end of study month 13	Red	Amber	Green
Total number of participants recruited	≤200	201–399	≥400
Recruitment of total required (%)	9	10–17	18
Average recruitment rate/site/active months in the best 60% of sites^*^	3	4	5
Number of sites open	<5	5–10	>10

*Sites recruitment rate will be calculated from site opening date.

If by the end of study month 19, overall recruitment is less than 1300 participants (58%), OR average recruitment rate/site/month is less than 6 participants in the best 60% of sites, OR there are less than 20 sites recruiting, we will further expand the number of NHS sites recruiting. We will also consider whether study extension is required.

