### Randomisation and interventions

Randomisation will be performed using a web-based randomisation service to ensure allocation concealment, managed by Edinburgh Clinical Trials Unit (ECTU). The allocation sequence will be created by an ECTU database programmer using computer-generated pseudo-random numbers. Participants will be randomised, 1:1, between the two study arms. Stratification by site will be used to ensure there will not be a significant imbalance between the number randomised to intervention and control at any site. Stratification by other site-level characteristics will not be performed.

Standard care will include all care usually given to unexplained syncope patients at each participating site along with some form of standard care monitoring such as but not limited to wired inpatient telemetry, Holter style monitoring or implantable ECG recorder. The study will be conducted over 4 years. Recruitment will take place over 18 months. Intervention group participants will be fitted with a 14-day ambulatory heart monitor. All participants will be followed up for 2 years after index event.

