#### Timelines

The study started on 1 August 2021 and the first patient was recruited on 15 July 2022. Recruitment is planned to end on 31 December 2023, the with study completing on 31 July 2025.

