#### Interim analysis

In addition to the blinded sample size review to ensure that the trial achieves the required statistical power, there will be a single interim futility analysis for the primary outcome performed after the 18th month of recruitment (end of study month 25). At this point 6 months of 1-year follow-up data will be available. We anticipate at least 400 participants will have undergone 12-month follow-up for the primary outcome at this point and will be able to be analysed in this futility analysis.

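### The recruitment and interim milestones, fixed by study month, do not fit the stated dates: study months 13, 19 and 25 end 1.5, 7.5 and 13.5 months after the first recruit, not 6, 12 and 18

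*Protocol article*

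**What the plan says.** Three sections of the protocol article bear on this.

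- **Study progression criteria.** "By the end of study month 13, the aim is to have 400 participants (18%) enrolled". In Table 3, a total of 200 or fewer is Red, 201 to 399 Amber and 400 or more Green. A second trigger follows at the end of study month 19: with fewer than 1300 participants (58%), the trial will add sites and consider an extension. Table 3 also has a per-site rate row, which its footnote counts from each site's opening, and a row for the number of sites open. The text sets ten open sites as the minimum, but Table 3 puts 10 sites in Amber and reserves Green for more than 10.
- **Timelines.** "The study started on 1 August 2021 and the first patient was recruited on 15 July 2022". Also: "Recruitment is planned to end on 31 December 2023". Completion is given as 31 July 2025.
- **Interim analysis.** The single futility analysis is to be "performed after the 18th month of recruitment (end of study month 25"). The section expects six months of one-year follow-up data by then, from at least 400 participants.

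The Randomisation and interventions section adds: "Recruitment will take place over 18 months".

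**The concern.** The milestones run on a study-month clock and the Timelines section gives calendar dates. The two can be compared directly, and they disagree by about four and a half months. The interim text shows that recruitment was expected to begin in study month 8, but it began in the middle of month 12. The dates in the article reflect the delay; the study-month milestones do not.

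The month-13 total feeds a stop-go decision intended to protect the funder, and the month-19 total decides whether sites are added. If both are read on the wrong clock, they mainly measure set-up delay. The same mismatch reaches the futility analysis, whose information content depends on how many participants have completed one year.

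**Working it through.** **Inputs.** Study start 1 August 2021, first recruit 15 July 2022, planned end of recruitment 31 December 2023, completion 31 July 2025 (Timelines); total 2234 (Sample size); 18 months of recruitment (Randomisation and interventions); thresholds 200, 400 and 1300 (Study progression criteria and Table 3); recruitment month 18 = study month 25 (Interim analysis). First recruitment is taken as first randomisation.

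**1. The plan's own percentages.** 400/2234 = 17.9% and 1300/2234 = 58.2%. Both match the stated 18% and 58%, so the thresholds are arithmetically sound. The issue is only when they apply.

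**2. The study-month clock.** 1 August 2021 to 31 July 2025 is 48 months, matching the stated four years, so study month 1 is August 2021. One month is taken as 30.44 days.
- Month 13 ends 31 August 2022: 47 days, or 1.5 months, after the first recruit.
- Month 19 ends 28 February 2023: 228 days, or 7.5 months.
- Month 25 ends 31 August 2023: 412 days, or 13.5 months.

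**3. The clock that the thresholds assume.** If recruitment month 18 is study month 25, recruitment month 1 is study month 25 − 17 = 8 (March 2022). Study months 13 and 19 are then recruitment months 6 and 12. The interim text supports this: participants with one-year data at recruitment month 18 are those recruited in the first six months, and the number expected, 400, is the month-13 target.

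**4. Expected totals at month 13.**
- Implied ramp (400 by recruitment month 6): 400/6 × 1.5 = 100. Red.
- Flat planned average: 2234/18 = 124.1 per month, × 1.5 = 186. With 17.5 months of recruitment: 127.7 per month, × 1.5 = 191. Exact day counts give 192 to 201, depending on the rate used and whether both end dates are counted. The range of 186 to 201 lies at the Red/Amber cut-off.
- Rate needed for Green: 400/1.54 = about 260 per month.
- Rate needed to leave Red: 201/1.54 = about 130 per month.

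**5. Expected totals at month 19.**
- Implied ramp: 400 + (1.5/6) × (1300 − 400) = 625.
- Flat average: 124.1 × 7.5 = 931, or 127.7 × 7.5 = 957.
- All are below 1300, which would need 1300/7.5 = 173 per month from the first day.

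**6. The interim analysis.** At 31 August 2023, one year of follow-up is complete only for those recruited by 31 August 2022. From step 4 that is about 100 to 200 participants, against the 400 anticipated. If the recruitment-month label is used instead, 18 months from 15 July 2022 is mid-January 2024, about two weeks after the planned end of recruitment. The two labels in that sentence now point to dates about 4.5 months apart.

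**The case against.** The calendar arithmetic is hard to dispute. The case on the other side concerns what follows from it, and much of it stands.

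- **A reader might infer that the pilot returns Red whatever the recruitment rate.** It does not. About 130 per month reaches Amber, only about 5% above the flat planned average. With the 30 to 40 sites foreseen under Participant recruitment, all open and recruiting five a month, 1.54 months would give 231 to 308, also Amber.
- **A reader might infer that the pilot cannot confirm recruitment rates, or that the trial as a whole would be classed Red.** The per-site rate row is counted from site opening and is untouched by the delay, and the sites-open row does not depend on time since the first recruit. The total and its percentage are affected, and they are one quantity. Table 3 gives no rule for combining rows, so one Red row does not settle the outcome.
- **Ten sites at five a month is a poor benchmark.** The rate criterion applies to the best 60% of sites only, and 10 × 5 × 6 = 300 is Amber even with six full months. It is not used here.
- **Month 19 has no Red class.** Missing 1300 leads to more sites and a possible extension, a reasonable response to a late start.
- **Timing and scope.** The article appeared on 23 February 2023, after month 13 and five days before the end of month 19. The funder or steering committee may have re-based the milestones; a condensed article cannot show this. Nothing here touches the estimand, the primary analysis or the sample size.

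These points limit the consequences. They do not make the printed milestones fit the printed dates, and the month-25 interim analysis was still ahead at publication.

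**Conclusion.** The point holds as an inconsistency between the milestones and the dates. Thresholds set for 6, 12 and 18 months of recruitment are attached to study months that end 1.5, 7.5 and 13.5 months after the first recruit. A trial on plan would show about 100 to 201 participants at month 13, far from Green and either in Red or at its upper edge, and about 625 to 957 at month 19, which fires the expansion trigger. At study month 25 it would have about 100 to 200 participants with one-year data rather than 400.

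These figures assume that study month 1 is August 2021, that recruitment follows either the implied ramp or a flat average, and that the study months were not reset elsewhere. Actual recruitment is not reported. The documents do not support an automatic Red or an overall failed pilot. The separate slip on ten sites is small but real: text and table classify the same number differently. This should be corrected, because it governs a stop-go decision and the content of a futility analysis, but it is a matter of trial governance rather than of the primary analysis.

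**What to change.** Restate the total-recruited, expansion and interim milestones as months since first randomisation: recruitment months 6, 12 and 18, which on the stated dates fall in mid-January 2023, mid-July 2023 and mid-January 2024. Reconcile the Timelines, Study progression criteria and Interim analysis sections so that each milestone carries one clock. For the interim analysis, state which label governs and the number with 12-month data expected at that date, noting that recruitment month 18 falls just after the planned end of recruitment. Where a milestone had already passed, record the clock on which it was judged. Align the site criterion, most simply by making Table 3 Green at 10 or more and Amber at 5 to 9.

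The cost is protocol wording and notification of the funder and the steering committee. No change to data collection, sample size or the primary analysis is needed.

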#### Data analysis plan

The primary outcome, number of self-reported episodes of syncope in the 12 months following randomisation, will be analysed by negative binomial regression. The primary outcome event rate ratio (14-day ambulatory heart monitor vs standard care) will be reported with its 95% CI. An offset term for follow-up duration will be included to account for participants with partial follow-up.

The secondary outcomes for the number of syncope episodes at 90 days and 2 years, will be analysed similarly. Binary secondary outcomes will be analysed by logistic regression, reporting the OR (14-day ambulatory heart monitor vs standard care) and its 95% CI. Full details of analysis, including the estimand(s) of interest and methods for handling missing data, will be written into a Statistical Analysis Plan, which will be finalised prior to database lock without knowledge of the unblinded treatment allocations.

#### Cost-effectiveness analysis

Anonymised electronic healthcare record data will be sent to our health economist in Sheffield to apply unit costs and tariffs, to estimate within trial costs and QALYs, and then to undertake lifetime economic modelling. Both within trial and lifetime cost-effectiveness analysis will be performed. In within trial analysis, costs will be estimated by applying national unit costs to items of resource use (monitoring, hospitalisation, treatment, health and social care) to estimate the mean cost per participant in each arm of the trial. Cost-effectiveness will then be estimated as the incremental cost per syncope episode avoided and the incremental cost per QALY gained, with QALYs being estimated from EQ-5D questionnaires. Lifetime cost-effectiveness will be estimated using decision analytic modelling from published sources of life expectancy, annual costs and corresponding annual utilities. This will explore the potential impact of events, such as syncope episode resulting in death or injury, that have consequences beyond the timeframe of the trial.

#### Interim analysis

In addition to the blinded sample size review to ensure that the trial achieves the required statistical power, there will be a single interim futility analysis for the primary outcome performed after the 18th month of recruitment (end of study month 25). At this point 6 months of 1-year follow-up data will be available. We anticipate at least 400 participants will have undergone 12-month follow-up for the primary outcome at this point and will be able to be analysed in this futility analysis.

### Patient and public involvement

The ASPIRED study patient and public involvement group is made up of patient representatives, lay members and a representative from the Arrhythmia Alliance. They have been involved in informing the study research questions and study protocol in particularly the methods and timings of patient follow-up, and the development of all patient facing information.

### Ethics and dissemination

The ASPIRED trial received a favourable ethical opinion from South East Scotland Research Ethics Committee 01 (21/SS/0073).

#### Participant capacity and consent

Capacity will be assessed by the research team or a clinician responsible for the treatment of the participant. The trial excludes patients who have inability to give informed consent and therefore patients with temporary incapacity due to their current illness or with permanent incapacity will not be recruited.

#### Safety considerations

##### Bias

The primary outcome is a quantitative endpoint (number of syncope episodes) collected through automated participant reporting importing directly into the ECTU central study database to reduce reporting bias. Central research staff who phone participants will be blinded to participant allocation.

##### Adverse events

A secondary endpoint for the study is serious outcomes at 90 days, 1 and 2 years. This data will therefore be routinely collected as part of the study and not recorded as an adverse event (AE). Hospital admission will also not be recorded as an AE. The only AEs recorded will be those directly related to the use of initial ambulatory ECG recording both in the intervention and standard care groups. Participants will be asked through the automated monthly email/text questionnaire at month 2, whether they suffered any complications related to wearing any monitoring devices in the first 2 months of the trial.

A Trial Steering Committee (TSC) will be established to oversee the conduct and progress of the trial. The details of the TSC will be captured in a separate charter. An independent Data Monitoring Committee (DMC) will be established to oversee the safety of participants in the trial. The details of the DMC will be captured in a separate charter.

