eCRF completion including demographic data and contact details	X						
Routine clinical care (eg, ECG)	X						
Randomisation		X					
Intervention group participants fitted with a 14-day ambulatory heart monitor		X					
Referral for syncope assessment and standard care monitoring as per local service protocol to be seen ideally within 4–6 weeks of the index event especially if discharged from ED or if this did not occur during index admission		X					
EQ-5D-5L questionnaires		X				X	X
NHS resource usage data from routine hospital electronic healthcare records extracted by the local study team)				X		X	X
Participant contacted on a 4-weekly basis via automated text message, email or phone with a link to a brief web-based questionnaire asking for the number of syncope events experienced since last response, and the number of GP attendances for any reason			X				
Participants not responding for 3 consecutive months to receive phone call from central study team to collect missing data, ensure no syncope episodes have occurred and to encourage continued future engagement. Participants with a mean of 5 or more episodes/month will also receive a phone call from the central study team to ensure that participants are recording true syncope events and are seeking appropriate medical advice					X		
Participant satisfaction questionnaire						X	

eCRF, electronic case report form; ED, emergency department; GP, general practitioner.

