All participants will be contacted on a 4-weekly basis ±14 days for 2 years via automated text message or email (whichever they prefer) with a link to a brief web-based questionnaire asking for the number of syncope events experienced since their last response and how many of these they attended hospital for. Those who are unable to access digital forms of communication will receive phone calls. They will also be asked since their last response how many times they have visited their GP practice for any reason including all face-to-face, telephone and online consultations. This will import directly into the central ECTU study database. This patient-reported data will be used to inform the primary endpoint. The small number of participants unable to access digital forms of communication and participants not responding for 3 consecutive months will receive a phone call from the central study team (blinded to participant’s study arm allocation) to collect missing data, ensure no syncope episodes have occurred and to encourage continued future engagement. Participants with a mean of 5 or more episodes/month will also receive a phone call from the central study team to ensure that participants are recording true syncope events and are seeking appropriate medical advice.

We were very thoughtful about the potential impact of COVID-19 when designing this study including ensuring ambulatory ECG monitors can be sent directly to patients and designing participant follow-up to ensure no additional research related hospital visits are required.

Participants will also be contacted at one and 2 years±30 days, by the central study team (blinded to participants study arm allocation) to complete a quality-of-life questionnaire. In the event of non-response, participants will be contacted on up to three occasions. The participants’ involvement in the study will cease at 2 years. Endpoint data including NHS resource usage will be extracted by the local study team from routine hospital electronic healthcare records at 90 days, 1 and 2 years and will be entered into a bespoke database. ECTU will collect and clean primary data and perform primary and secondary analyses.

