#### Sample size

Two thousand two hundred and thirty-four participants (1117 standard and 1117 intervention) presenting acutely with syncope whose syncope remains unexplained after initial ED/AMU assessment will be recruited. Using an estimated mean 1-year recurrence rate in untreated patients of 42.5%^6^ and a reduction in 1-year recurrence rate to 10% in patients who are treated^11 19^ then the hypothesis is a 1-year recurrence rate in the standard group (2% diagnosed with a symptomatic significant arrhythmia with 90% of these expected to not have recurrence after treatment) of 40.7% compared with a recurrence rate of 33.1% in the treatment group (10.5% of pilot participants diagnosed with symptomatic significant arrhythmia at 90 days with 90% of these expected to not have recurrence after cardiac arrhythmia treatment) equating to an event rate ratio of 0.81. A more conservative effect size of 6% (40% vs 34%) will be assumed corresponding to a more conservative event rate ratio of 0.85. A large study of unexplained untreated syncope patients^20^ suggests a median (IQR) number of events in the preceding 2 years of 3 (2–4) with a median (IQR) per year of 2 (1–3.5). The ESC guidelines^6^ suggest that the number of events has a good fit to a Poisson distribution and the untreated event rate postattendance is about 70% reduced from the preattendance rate. The ESC guidelines^6^ and PICTURE^20^ suggest a mean number of events per participant of approximately 1 during 1 year of follow-up. If we assume that this follows a negative binomial distribution (which allows for ‘over dispersion’ vs the Poisson distribution) then a study of 1064 participants per group would have 90% power (two-sided significance level=5%, over dispersion=0.25) to detect an event rate ratio of 0.85.

The study will recruit an extra 5% in each arm (ie, 1117 participants per arm; 2234 in total) to allow for drop-out/loss to follow-up although we expect this to be low (<1% in pilot) and drop out due to death (<1% in pilot). It is expected that most people will respond to some text/email follow-ups, but few will respond to all. We will therefore call any participant who has not responded for 3 consecutive months to ensure no syncope episodes have occurred and to encourage continued future engagement. Participants will be defined as lost to follow-up only if both 1-year electronic patient health record data and 1-year self-reported data are unavailable.

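### Device complications are asked about once, at month 2, so these data are likely to be incomplete and may be captured unequally by arm

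*Protocol article*

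**What the plan says.** Under Safety considerations, Adverse events, the protocol article sets the scope: "The only AEs recorded will be those directly related to the use of initial ambulatory ECG recording both in the intervention and standard care groups". The same paragraph gives the method: "Participants will be asked through the automated monthly email/text questionnaire at month 2, whether they suffered any complications related to wearing any monitoring devices". The recall period for this item is two months from entry. The article describes no other means of asking participants about complications. In Table 2 the monthly contact covers syncope events and GP attendances only.

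On response, the Sample size section states: "It is expected that most people will respond to some text/email follow-ups, but few will respond to all". The follow-up text under Trial assessments says that "participants not responding for 3 consecutive months will receive a phone call from the central study team", the purpose being "to collect missing data, ensure no syncope episodes have occurred and to encourage continued future engagement". Participants without digital access are telephoned routinely. Contacts are four-weekly, ±14 days. The syncope question asks for events since the last reply, so a missed month is picked up at the next one.

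On timing, the patch is applied as soon as possible after randomisation and worn for at most 14 days. Randomisation is within 72 hours of attendance. Referral for syncope assessment and standard-care monitoring is "to be seen ideally within 4–6 weeks of the index event" (Table 2), particularly for participants discharged from the ED or not assessed during the index admission. No upper limit is given. Both arms are referred. Standard care may also be inpatient telemetry, a Holter-type device or an implanted recorder (Randomisation and interventions).

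**The concern.** The stated aim is to record events "directly related to the use of initial ambulatory ECG recording both in the intervention and standard care groups". The method described may miss part of this in two ways.

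- **Non-response.** The item is tied to one contact. Unlike the syncope count, it has no described catch-up. Someone who misses month 2 but answers months 1 and 3 never triggers the call.
- **Timing of exposure.** The wording and calendar window are the same in both arms, but the devices need not be worn at the same time. The patch falls early in the window. A first standard-care monitor may come late in it, or after it. A control who has not yet worn a device and reports no complication would then be indistinguishable from one who wore a device without trouble.

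At stake is the only described source of device-harm data, which bears on adoption of the patch and on the Data Monitoring Committee's view of tolerability.

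**Working it through.** The plan gives no figure for month-2 response, complication rate or timing of control monitors, so there is none of its own to reproduce on this point. The denominator is the plan's 1117 per arm (1064 × 1.05 = 1117.2). The sample size calculation does not enter the argument.

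**Step 1: participants with no answer to the item**

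Assumptions: each digital user misses any contact with probability q, independently across contacts. q runs from 0.2 to 0.5 (response 80% to 50%). The three-month call always succeeds and includes the item, which the article does not say explicitly.

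A person who misses month 2 gets a call that covers it only by missing months 1–3 or months 2–4:

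- P(month 2 missed) = q
- P(month 2 missed and recovered by the call) = q³ + q³ − q⁴ = q³(2 − q)
- P(no answer) = q − q³(2 − q)

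| q | Month 2 missed | Recovered by call | No answer | Of 1117 per arm |
|---|---|---|---|---|
| 0.2 | 20% | 0.008 × 1.8 = 1.4% | 18.6% | about 207 |
| 0.5 | 50% | 0.125 × 1.5 = 18.8% | 31.3% | about 349 |

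The call recovers little when response is good, because isolated misses do not trigger it.

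**Step 2: the item carried forward over contacts 2 to 5**

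P(no answer) = q⁴, before any call:

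- q = 0.2: 0.2⁴ = 0.16%
- q = 0.5: 0.5⁴ = 6.3%

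Anyone missing all four contacts has also missed three in a row, so a call that names the item would reach them too, if it succeeds.

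**Step 3: timing of devices against the question**

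- Month-2 contact: day 56 ± 14, that is day 42 to 70.
- Recall window: two months, about 56 to 61 days.
- Patch: randomised by day 3 and applied promptly, worn to about day 14 (3 + 14 = 17 at the latest, before any postal delay). Well inside the window.
- Standard-care assessment at the stated target: day 28 to 42. A 14-day device (assumed) started at day 42 ends at day 42 + 14 = 56, just inside.
- The same participant, contacted at day 42, would be asked before wearing the device.
- A first device started after about day 61 lies wholly outside the window.

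**Step 4: what unequal capture could do (illustration only)**

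Suppose the true complication risk is equal, all patch complications fall inside the window, and a share d of control complications does. The apparent patch-to-control ratio among those who answer is 1/d: 1.0 at d = 1, 1.25 at d = 0.8, 1.43 at d = 0.7 and 2.0 at d = 0.5. The documents give no value for d.

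**The case against.** Several counter-arguments stand, and they limit the point.

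- **Safety more broadly.** A reader might infer that the trial's only safety comparison is lost. The documents do not support that. All-cause death is compared by arm at 30 days, 1 year and 2 years, and serious outcomes are collected separately at 90 days, 1 and 2 years. Only device-wearing complications are at issue, and these are not a listed secondary endpoint.
- **Direction.** A reader might also infer that the comparison is tilted against the patch. That is not established. Inpatient or early monitoring falls inside the window, and monitoring at the target time mostly does. Both arms are referred, and both get the same question about any device.
- **Size of the gap.** It is tempting to read all month-2 non-responders, 20–50% on the assumed rates, as never asked. They are sent the question, and the call after three missed months is meant to collect missing data, which reduces the range as in Step 1. If non-response clusters within persons, more of them trigger the call and the figure falls further; unsuccessful calls would raise it.
- **Other routes.** The article does not say that the questionnaire is the only adverse event route. The full protocol may describe others, or may already make an unanswered item reappear.
- **The remedy.** Repeating the item only until a device has been worn would give controls more prompts and a shorter recall, creating an imbalance of its own. This is a fair objection, and the fix must be the same in both arms.

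What remains is that, followed as written, an isolated month-2 miss is not recovered and a late first control monitor is not covered.

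**Conclusion.** The point holds as a modest, inexpensive improvement. Device-complication data are likely to be incomplete: about 19–31% without an answer if 50–80% respond at each contact independently and the three-month call always collects the item. These rates are assumptions; the article says only that few will answer every contact. Capture may also differ by arm, because some first standard-care monitors may be worn after the question or its window. Neither the size nor the direction of any difference can be derived from the document. The primary outcome, the sample size, death and serious outcomes are not affected.

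**What to change.** 1. In both arms, carry the complication item forward from month 2 to each later contact until it has been answered once.
2. Name the item among the missing data to be collected at the existing three-month non-response call.
3. In both arms, add a yes/no on whether a monitoring device has been worn since joining the study, and when. Repeat this with the complication item for everyone at one fixed further contact, regardless of arm or earlier answer. Late first monitors are then captured, and a report of no complications from someone not yet monitored is not counted as a harmless device.

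If the full protocol already does any of this, it is enough to say so.

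The cost is a small change to questionnaire logic and one or two extra items at a later contact. Some participants will have a somewhat longer recall period. Recruitment was planned to run to the end of 2023, after the article appeared, so a change made then could still have reached later participants.
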